#### iv) To examine the costs of the Ebola+D mental health intervention.

The data collection team will consist of a health economist and a health economics research assistant. Cost data collection will be undertaken over a 3-month period using a standardized Excel based cost data collection tool that will be developed by the research team. Published literature will be reviewed to identify the cost categories used by similar previous studies when developing the tool. In addition to this, the health economics research team will review the Ebola +D mental health intervention documents to develop a cost category list for the program. The developed tool will be piloted in one health facility and tool modifications will be made before costing the remaining 5 health facilities.

### Resources/ Inputs

To determine the costs from the providers’ perspective, the value and quantity of resources/ inputs required to produce outputs like outpatient visits for screening, treatment and follow-up are required. These inputs will be categorized into three, start-up costs, personnel costs and operational costs as provided in Table 2.

**Table 2 pone.0329591.t002:** Summary of cost data to be obtained.

Cost Category	Information to be obtained	Data Source
**A. START-UP COSTS**		
**Health Worker Training** Training costs per participant (Lay health workers, clinician and mental health specialist)	- Duration of training (number of days) - Number of health workers trained and their cadre - Transport costs to attend trainings - Accommodation costs - Training materials such as therapy manuals - Costs of hiring training venue - Costs of supplies for training such as pens, notebooks, food - Number of refresher trainings - Costs of trainers (if applicable) - Hiring costs (if applicable)	Project Training Records
**Furniture and Equipment**	Costs of tables, chairs, metallic cabins and umbrellas that will be delivered to the various health facilities.	-Project Records -MRC procurement records

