### Steps in the development of the Ebola+D mental health intervention

The development of the Ebola+D mental health intervention was guided by prior experience of the Mental Health Research Team (which included psychologists, psychiatrists, social workers and health economists) who had participated in the HIV + D trial and in the initial psychosocial response to the Ebola epidermic in Mubende district. Through a series of meetings by the Mental Health Research team a number of factors were noted, namely: i) the lack of primary mental health services in the target district; ii) the severe shortage of mental health workers in the district; iii) the severe shortage of medical personnel in the primary health facilities; iv) the fact that the community was struggling to cope with the negative consequences of the Ebola epidermic which occurred right on the heels of the COVID-19 pandemic, the team thought that the community would benefit from problem solving training rather than behavioural activation which had earlier been successfully used in the HIV + D trial; and v) the fact that the HIV + D stepped care collaborative model had been able to successfully circumvent the above challenges in HIV care. We therefore opted to adapt the HIV + D mental health intervention into the local situation in Mubende district through the following five phases: i) adapt the HIV + D collaborative stepped care mental health intervention into primary health care in Mubende district to produce the Ebola+D mental health intervention; ii) to adapt and translate the Problem Solving Therapy for Primary Care (PST-PC) treatment manual [33] to the local rural situation in Mubende district; iii) a pilot study to evaluate the acceptability, feasibility and impact on mental health outcomes of the Ebola+D mental health intervention; iv) a health economics component to examine the costs of the Ebola + D mental health intervention from the providers’ perspective to determine how much it will cost for the health system to set up and operate the intervention at the health facility level.; and v) to explore the Ebola virus disease (EVD) associated negative beliefs and lived out experiences of affected members of the community.

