**C. OPERATIONAL COSTS**		
**Capital- Building Space** (Costs for space utilized by the Ebola+D intervention)	- Where are health talks given? - Where are the patients screened, enrolled and treated from? - Where are the tests conducted? - How many square meters are the facility? - What is the value of the facility? - What are the maintenance costs?	Direct measurements of building space utilized by the intervention
**Capital – Equipment** (Costs of Equipment utilized by the Ebola+D intervention)	- What equipment are used for the tests carried out? - What is the price of the equipment used? - What are the maintenance costs for the equipment?	-Facility Accountant -Facility Administration records
**Drugs** (Costs of recurrent drugs used in the intervention)	- What drugs are used to manage mental health problems? - What is the origin (producer) - What is the dose and strength of the drug? - What is the mode of administration? - What is the cost of the drug?	National Medical Stores price list
**Supplies** (Costs of recurrent supplies used in the intervention)	- What supplies are used for tests (such as pregnancy tests)? - What supplies are used for screening, enrolment, treatment? - What are the costs of these supplies?	-MRC Project Records -Health Facility Records -National Medical Stores price lists.
**Utilities** (Cost of overhead costs)	What are the recurrent expenditures for electricity, water, internet, telephone/ airtime for the most recent financial year?	Facility Accounts records

Start-up costs include the costs of activities and equipment needed when setting up the intervention (these are a one-off expenditure). Personnel category includes the cost of all staff involved in the delivery of the Ebola+D mental health intervention, while the operational cost category includes the cost of all items that are related to operational activity of the intervention**.**

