### Direct costs

Direct medical costs of treatment will be disaggregated and descriptively analysed from baseline to endline. Categories of cost-related data will be assessed to determine the major cost drivers for delivering mental health services for EVD affected communities.

All research costs and start-up costs will be reported separately from the cost of delivering the intervention.

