### Provider cost measurement and valuation

The quantity of resources used, and their respective unit costs will be used to calculate the unit cost for each service output such as, outpatient visits (including screening, consultation, treatment and follow-up visits), inpatient bed days and medication. The function below explains the calculation of the service output unit cost.

OUC=n(R) ×p(R)\]

Where OUC is the unit cost per service output, n(R) is the quantity of resources used and p(R) is the unit cost of resources used [53,54].

The total unit cost per patient will be calculated by multiplying the quantity of each service output by the unit cost of the service output from screening to the end of treatment for each patient in the study. The function below explains the calculation of the total unit cost per patient.

TUC=q(S)×OUC\]

Where TUC is the total unit cost per patient, q(S) is the quantity of each service output and OUC is the unit cost per service output [53,54].

The average cost per patient for screening and treatment will be derived and compared across 6 facilities using a t test.

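### Refresher training is classed as a one-off start-up cost, so any refresher held after set-up falls outside the delivery cost

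*Protocol article*

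**What the plan says.** The costing component is meant to "determine how much it will cost for the health system to set up and operate the intervention at the health facility level" (Steps in the development of the Ebola+D mental health intervention). The Resources/Inputs section sets the classification: "These inputs will be categorized into three, start-up costs, personnel costs and operational costs as provided in Table 2".

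In Table 2, the Health Worker Training row stands in section A, start-up. It asks for training days, numbers and cadres trained, transport, accommodation, materials, venue, supplies and trainers, and also for the "Number of refresher trainings".

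The paragraph below the table gives the definitions:
- Start-up: "Start-up costs include the costs of activities and equipment needed when setting up the intervention (these are a one-off expenditure".
- Personnel: "Personnel category includes the cost of all staff involved in the delivery of the Ebola+D mental health intervention".
- Operational: "the operational cost category includes the cost of all items that are related to operational activity of the intervention".

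The Direct costs section then states: "All research costs and start-up costs will be reported separately from the cost of delivering the intervention".

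**The concern.** A refresher by its nature follows initial training and can be repeated, and the table itself asks how many there were. It fits poorly in a category defined as spent once, at set-up. Because that category is kept apart from the delivery cost, following the plan as written would put a repeatable cost into the set-up figure and leave it out of the running figure.

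The split matters here because the stated purpose has two parts, setting up and operating. A health ministry deciding whether to sustain the programme needs the second part. The article also treats keeping lay workers competent as a continuing task. Its account of services during the outbreak notes that no arrangement existed to go on supporting trained village health team members. The theory-of-change workshops are to discuss how competencies will be kept up as well as acquired. Refresher training is one obvious way of doing that, so its place in the accounts is not arbitrary.

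**Working it through.** The article states no cost figure, so there is none to reproduce. The check follows the item through the costing sections and then expresses the effect in symbols.

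**Tracing the item**
1. Table 2, section A: refresher training is one entry in the Health Worker Training row, under start-up.
2. Definition below Table 2: start-up is one-off.
3. Direct costs: start-up is reported apart from the delivery cost.
4. Table 2, section B (personnel): the entries concern services delivered, such as health talks, screening, psychoeducation, problem-solving therapy and reviews. There is no training entry.
5. Table 2, section C (operational): the rows are building space, equipment, drugs, supplies and utilities. There is no training row.
6. Provider cost measurement and valuation: "The total unit cost per patient will be calculated by multiplying the quantity of each service output by the unit cost of the service output". The named outputs are outpatient visits, inpatient bed days and medication. Training is not among them.
7. Time study: the activity log is for staff time on intervention activities, and the duties it names are delivery and prescribing. The list is illustrative, so hours spent at a refresher could be logged there. Transport, venue, materials and trainers would not be.
8. Sensitivity analysis and uncertainty: the most and least expensive scenarios vary cost components such as lay-worker salaries. They do not move an item between categories.

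Nothing in steps 4 to 8 assigns the cost of refresher training to delivery.

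**Effect in symbols**

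Let S be the start-up cost without refreshers, D the delivery cost as planned (personnel plus operational), k the number of refresher rounds held after set-up, and c the cost per round.

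| | As classified | Refreshers as recurrent |
|---|---|---|
| Set-up | S + k·c | S |
| Operate | D | D + k·c |
| Total | S + D + k·c | S + D + k·c |

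- Shortfall in the operating figure: (D + k·c) − D = k·c.
- As a share of the reclassified operating cost: k·c / (D + k·c).
- If k = 0, the shortfall is 0. If k ≥ 1 and c > 0, it is positive.
- The total is the same in both columns.

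The article gives no value for k, c or D, so no amount follows. A per-patient figure would also need a settled denominator. The sample size section fixes 1,000 participants, whereas at least 100 from each of 11 facilities gives 11 × 100 = 1,100, and the provider costing covers only 6 facilities.

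**The case against.** The strongest reply is that Table 2 lists data to be collected and is not a costing rule. Refreshers may sit in the training row only because all training data come from the same project training records. The categories are also not final: the data collection text for the costing objective says that a cost category list and an Excel tool are still to be developed, piloted in one facility and modified before the other five are costed. No sentence says outright that refreshers are treated as one-off, and no schedule shows that they will recur. Refreshers held during roll-out could fairly count as set-up.

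Part of this stands. The effect is conditional on refreshers being held after set-up, and the tool can still be designed to avoid it. But Resources/Inputs says that inputs will be categorised as in Table 2, so the table does fix the classification unless it is changed.

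A reader might infer two stronger things. One is that the running cost is definitely understated, or that a cost is lost. The documents do not support this: no refresher schedule is given, and start-up is reported separately, not discarded. The other is a monetary amount per patient. That would rest on an invented refresher frequency and price, and on a trainee count that has to include the mental health specialist whom Table 2 lists among those trained.

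**Conclusion.** The point holds as a conflict between a table entry and the definition that governs it. Any refresher training held after set-up would be counted as set-up and left out of the delivery cost, by the full amount k·c. This shifts the set-up/operate split that the costing is meant to provide and leaves the combined total intact. The conclusion assumes that Table 2 is applied as printed and that at least one refresher follows set-up. The size is unknown and may be small. The costing is a descriptive component, and no clinical outcome, power figure or test of effect depends on it. It is a minor correction.

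**What to change.** Keep initial training in Table 2, section A. Class refresher training as a recurrent cost, under personnel or operational, and include it in the delivery cost per patient.

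Moving the single entry is not enough, because it is only a count. The days, transport, accommodation, venue, materials and trainer entries in that row are not split by type of training, so the costs would stay behind in start-up. The cost tool should record these inputs separately for initial and refresher training. If some refreshers are regarded as part of roll-out, the plan should say where set-up ends.

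The cost is slightly more detailed recording from the project training records. As the tool is still to be developed and piloted, the change is easiest to make now.

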**B. PERSONNEL COSTS**		
**Service delivery costs** Cost for each service delivered by the different health workers involved in the study such as trained lay health workers, clinicians and specialized mental health specialists, phlebotomists	- How many health talks were given? - How many people attended the health talks? - How many patients were screened? - How many patients were enrolled in the study? - How many patients are receiving psychoeducation? - How many patients are receiving problem-solving therapy? - How many times do they review patients receiving treatment? - What is the average time spent delivering treatment to patients? (number of minutes/hours) - How many mental health distress related inpatient bed days were recorded at the facility? - How many patients were suicidal? - How many patients were receiving SSRIs?	-Time study -Facility Data Managers -Intervention Data
**C. OPERATIONAL COSTS**		
**Capital- Building Space** (Costs for space utilized by the Ebola+D intervention)	- Where are health talks given? - Where are the patients screened, enrolled and treated from? - Where are the tests conducted? - How many square meters are the facility? - What is the value of the facility? - What are the maintenance costs?	Direct measurements of building space utilized by the intervention
**Capital – Equipment** (Costs of Equipment utilized by the Ebola+D intervention)	- What equipment are used for the tests carried out? - What is the price of the equipment used? - What are the maintenance costs for the equipment?	-Facility Accountant -Facility Administration records
**Drugs** (Costs of recurrent drugs used in the intervention)	- What drugs are used to manage mental health problems? - What is the origin (producer) - What is the dose and strength of the drug? - What is the mode of administration? - What is the cost of the drug?	National Medical Stores price list
**Supplies** (Costs of recurrent supplies used in the intervention)	- What supplies are used for tests (such as pregnancy tests)? - What supplies are used for screening, enrolment, treatment? - What are the costs of these supplies?	-MRC Project Records -Health Facility Records -National Medical Stores price lists.
**Utilities** (Cost of overhead costs)	What are the recurrent expenditures for electricity, water, internet, telephone/ airtime for the most recent financial year?	Facility Accounts records

Start-up costs include the costs of activities and equipment needed when setting up the intervention (these are a one-off expenditure). Personnel category includes the cost of all staff involved in the delivery of the Ebola+D mental health intervention, while the operational cost category includes the cost of all items that are related to operational activity of the intervention**.**

### Direct costs

Direct medical costs of treatment will be disaggregated and descriptively analysed from baseline to endline. Categories of cost-related data will be assessed to determine the major cost drivers for delivering mental health services for EVD affected communities.

All research costs and start-up costs will be reported separately from the cost of delivering the intervention.

### Provider cost measurement and valuation

The quantity of resources used, and their respective unit costs will be used to calculate the unit cost for each service output such as, outpatient visits (including screening, consultation, treatment and follow-up visits), inpatient bed days and medication. The function below explains the calculation of the service output unit cost.

OUC=n(R) ×p(R)\]

Where OUC is the unit cost per service output, n(R) is the quantity of resources used and p(R) is the unit cost of resources used [53,54].

The total unit cost per patient will be calculated by multiplying the quantity of each service output by the unit cost of the service output from screening to the end of treatment for each patient in the study. The function below explains the calculation of the total unit cost per patient.

TUC=q(S)×OUC\]

Where TUC is the total unit cost per patient, q(S) is the quantity of each service output and OUC is the unit cost per service output [53,54].

The average cost per patient for screening and treatment will be derived and compared across 6 facilities using a t test.

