**Fig 1 pone.0329591.g001:**
[figure not shown]
Ebola+D study flowchart.

Eligibility criteria for participating in this study: i) Community member of Mubende district staying within the catchment area of the PHCF; ii) 18 years and above, iv) able to communicate in either English or Luganda (local language spoken in the study region and the language into which the questionnaires will be translated), v) has a WHO SRQ-20 score of 6 and above.

Exclusion criteria: i) unable to engage with the research process for any reason that may include sensory impairment or cognitive impairment.

The study aims to enrol at least 100 respondents with psychological distress (SRQ-20 score ≥ 6) from each of the 11 participating PHCFs. Enrolled respondents will be provided with PST at bi-weekly sessions. Monthly assessments will be undertaken to monitor their level of psychological distress using the SRQ-20 until psychological distress scores have fallen to less than 6. A patient will be declared in remission if after completing their prescribed therapy (PST or medication) they remain symptom free (SRQ-20 scores of less than 6) on two occasions one month apart. A full complement of supporting and resource materials including clinic posters, health worker aide-memoire, and patient and care-giver resource materials will be developed and evaluated. The reporting of the trial will be in accordance with the SPIRIT guidelines for interventional trials [40] (S1 File).

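### The per-patient cost formula counts only an enrolled patient's own screening, so the figure compared across six facilities omits the screening of people who score below 6

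*Protocol article*

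**What the plan says.** The aim of the costing component, in *Steps in the development of the Ebola+D mental health intervention*, is "to determine how much it will cost for the health system to set up and operate the intervention at the health facility level". Objective 4 under *Participants and procedure* names the estimate as an average total unit cost per patient covering both screening and treatment. It adds that top-down and bottom-up approaches will both be used and that provider costs will be summed to a per-patient figure.

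The calculation itself appears only in *Provider cost measurement and valuation*. The total per patient comes from "multiplying the quantity of each service output by the unit cost of the service output from screening to the end of treatment for each patient", restricted to patients in the study. The symbols are defined so that "TUC is the total unit cost per patient, q(S) is the quantity of each service output and OUC is the unit cost per service output". The outputs given as examples are "outpatient visits (including screening, consultation, treatment and follow-up visits), inpatient bed days and medication". The resulting average is then compared across the six costed facilities.

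To be a study patient, a person must meet the eligibility criteria under objective 3, one of which is that he or she "has a WHO SRQ-20 score of 6 and above". Table 2, part B, keeps the two counts apart: "How many patients were screened? - How many patients were enrolled in the study".

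**The concern.** The service finds its patients by screening. Every screen uses staff time and supplies whatever its result, so screening people who turn out negative is part of the recurrent cost of operating the intervention. In the formula, an output counts only if a study patient received it. A person who scores below 6 is not a study patient, so that person's screen belongs to no patient's q(S). No other term in the formula brings it back.

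Two things are at stake. First, a planner who multiplies the per-patient figure by an expected number of treated patients would leave out part of the cost of finding them. Second, a facility that screens ten people to find one case and a facility that screens two would show the same screening cost per patient. The six-facility comparison would then be blind to a possible cost driver, although *Direct costs* promises to identify the major ones.

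Health talks raise a related question. They are given to everyone waiting at triage and are counted in Table 2, but they are not among the example outputs and no rule allocates their cost.

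**Working it through.** The protocol article states no cost figure, screening yield or unit cost, so there is no figure to reproduce. The check is algebra on the written rule, followed by illustrative values.

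**Inputs from the document**
- Cost rule: quantity of each output times its unit cost, for study patients only (*Provider cost measurement and valuation*).
- Entry condition: SRQ-20 of 6 or more (eligibility criteria, objective 3).
- Enrolment target: at least 100 per facility (objective 3), with six facilities costed (objective 4).

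**Assumed inputs**
- c = cost of one screen.
- T = all other costs per treated patient, in multiples of c: 5, 10, 20 or 50.
- y = share of screened people who score 6 or more: 0.1 to 1. For the illustration, everyone who scores 6 or more is enrolled and treated.

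**Formulas**
- As written: cost per patient = c + T, which does not contain y.
- With all screening charged to treated patients: c/y + T, because 1/y people are screened for each one found.
- Shortfall: (c/y + T) − (c + T) = c(1/y − 1). It is zero at y = 1 and positive at any lower yield.
- Shortfall as a share of the full cost: c(1/y − 1) / (c/y + T).

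**Worked cases**
- y = 0.5, T = 20c: 21c as written, 22c in full; 1/22 = 4.5%.
- y = 0.3, T = 10c: 11c as written, 13.33c in full; 2.33/13.33 = 17.5%.
- y = 0.1, T = 5c: 6c as written, 15c in full; 9/15 = 60%.

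**Understatement of cost per treated patient over the assumed range**

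| y | T = 5c | T = 10c | T = 20c | T = 50c |
|---|---|---|---|---|
| 1.0 | 0% | 0% | 0% | 0% |
| 0.8 | 4.0% | 2.2% | 1.2% | 0.5% |
| 0.5 | 14.3% | 8.3% | 4.5% | 1.9% |
| 0.3 | 28.0% | 17.5% | 10.0% | 4.4% |
| 0.2 | 40.0% | 26.7% | 16.0% | 7.3% |
| 0.1 | 60.0% | 45.0% | 30.0% | 15.0% |

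**Number of uncounted screens.** With 100 enrolled at each of six facilities (600 in all), screens of people below 6 number 600/y − 600: 150 at y = 0.8, 600 at y = 0.5, 1,400 at y = 0.3 and 5,400 at y = 0.1.

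**The case against.** The strongest reply is that the plan does capture these costs. Table 2 counts people screened, health talks given and people attending them, and lists the space and supplies used for screening. The text after the table includes the cost of all delivery staff. The *Time study* records staff time on intervention activities. Objective 4 adds top-down costing, and *Sensitivity analysis and uncertainty* calculates programme costs. A top-down total would contain the negative screens. The formulas are also schematic, and a condensed article may leave allocation rules to a fuller document.

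Much of this stands. A reader might infer that the cost of negative screens is lost from the plan, or that the whole costing is understated. The documents do not support that: the resources and counts are collected, and other parts of the costing could carry them. What the reply does not remove is that objective 4 defines no denominator, the programme-cost section gives no allocation, and the one rule that is stated covers study patients only. That is a stated rule that misses its stated target, not merely an omitted detail.

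The size is also open. A reader might infer a large understatement by assuming low yields. Objective 3, however, describes those screened at the study facilities as people already accessing mental health services, among whom yield could be high. *Ebola+D mental health intervention* speaks of screening community members more broadly, which would suggest a lower yield. The documents do not settle it. Nor do they show that yield differs between the six facilities, so distortion of that comparison is possible rather than demonstrated. The sensitivity section names lay health workers' salaries only as an example and does not single out screening.

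**Conclusion.** The point holds for the per-patient figure. As written, it counts an enrolled patient's own screening, omits the screening of people who score below 6, and is unaffected by yield. That does not match the aim of costing the operation of the intervention for the health system, nor an estimate described as covering screening and treatment.

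The direction is certain for a cost per treated patient whenever anyone screens negative. The size cannot be fixed from the document. It is c(1/y − 1), which is negligible if nearly everyone screened scores 6 or more, or if treatment costs far more than a screen. It is material only when yield is low and other costs are modest. Every percentage above rests on assumed values of y and T. The conclusion is that objective 4 and *Provider cost measurement and valuation* need to be reconciled with the stated aim, not that the costing as a whole fails.

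**What to change.** In *Provider cost measurement and valuation*:
- State the denominator of the per-patient cost, and make objective 4 agree with it.
- Report cost per person screened and cost per person treated separately.
- For cost per person treated, replace the patient's single entry screen at each facility by (number screened / number scoring 6 or more) × unit cost of a screen.
- Use the number scoring 6 or more rather than the number enrolled. Enrolment also reflects consent refusals and research exclusions, and *Direct costs* requires research costs to be reported separately.
- Report health-talk cost as its own facility-level line, with any allocation stated. The talks serve everyone at triage, so charging them all to treated patients would need a justification.

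In *Sensitivity analysis and uncertainty*, add screening yield to the quantities varied between scenarios.

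The cost is small. Table 2 already collects "How many patients were screened" and "How many patients were enrolled in the study". The number scoring 6 or more is one further count, for which the screening logbooks named in Table 1 are the natural source. The stated cost per treated patient becomes somewhat higher, and there is slightly more analysis work.

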### Sample size and power calculations

The study will be longitudinal, with participants followed over a 12-month period. Psychological distress will be assessed using the SRQ-20, with a score of 6 or higher indicating distress. The primary outcome of interest will be remission of distress, defined as an SRQ-20 score below 6. All participants enrolled at baseline will have a level of distress. The intervention is hypothesised to reduce distress prevalence by at least 25%.

Given the longitudinal design and the use of clinic-based interventions, clustering effects will be accounted for by applying a design effect of 1.2, which reflects improved clustering control. Statistical parameters will include a confidence level of 95%. The total sample size will be fixed at 1,000 participants, requiring adjustments to the effective sample size to account for clustering.

The power calculation will be performed using a z-test for two proportions to compare the baseline and post-intervention prevalence of distress.

Using the assumed 25% absolute reduction in distress prevalence, the adjusted effective sample size of 1,000 participants, and a two-tailed significance level of 0.05, the estimated power of the study is calculated to be 94.5%.

Given the 12-month follow-up period and the community-based nature of the intervention, we anticipate an attrition rate of approximately 15%, based on evidence from similar longitudinal studies in rural Ugandan settings. Despite the anticipated attrition, the study will maintain the recruitment target at 1,000 participants, acknowledging that some loss to follow-up is expected. The analysis will account for missing data through multiple imputation techniques and sensitivity analyses to ensure that the study maintains sufficient power and validity to detect the hypothesized effect size.

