#### 4) To examine the costs of the Ebola + D mental health intervention.

A subset (n = 6) of the Ebola +D study facilities will be selected for the provider costing using a multi-stage stratified random sampling approach based on facility level and catchment population. We will estimate the average total unit cost per patient for screening and treatment of mental health disorders at the health facilities in Mubende district. A combination of retrospective and prospective methods of cost data collection will be used. Both macro (top-down) and micro (bottom-up) costing approaches will be applied. The disaggregated provider costs will be summed to produce a unit cost per patient for screening and treatment of mental health problems from the provider perspective.

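### A t test is named for comparing cost per patient across six facilities, but it compares only two means and no two groups are defined

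*Protocol article*

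**What the plan says.** The analysis sentence is in the protocol article under Provider cost measurement and valuation: "The average cost per patient for screening and treatment will be derived and compared across 6 facilities using a t test". The section gives no pairing, contrast or multiplicity rule for it.

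The number of facilities is consistent throughout. Under Participants and procedure, item 4, "A subset (n = 6) of the Ebola +D study facilities will be selected for the provider costing". Under Data collection, item iv, the costing tool is piloted in one facility and "tool modifications will be made before costing the remaining 5 health facilities", which again makes six.

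The six are chosen by a "multi-stage stratified random sampling approach based on facility level and catchment population". Those strata serve to select sites; they are not named as the groups for the test. Cost is built up per patient, "from screening to the end of treatment for each patient in the study", so there is variation within each facility and a test can be computed.

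**The concern.** The article names a specific test, and that test cannot carry out the comparison it is attached to. This is not detail left to an analysis plan. A two-sample t test handles two means; six facilities need either a multi-group test or a stated reduction to two groups. With neither, an analyst following the sentence would most naturally test every pair of facilities.

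What is at stake is any statement that one facility costs more per patient than another. Costing is one of the five study phases and is meant to show what it costs the health system to set up and run the intervention at facility level. A chance difference between facilities could be reported as real in that context.

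**Working it through.** The article gives no error rate, power or sample size for the cost comparison, so there is no stated figure to reproduce. The check asks what the sentence implies if applied literally.

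**Inputs**
- Facilities: 6 (item 4; confirmed as 1 pilot + 5 remaining in item iv).
- Level per test: two-sided 5%. The article gives "a two-tailed significance level of 0.05" under Sample size and power calculations, for the primary outcome only. Using it for costs is an assumption.
- Patients per facility: "at least 100 respondents with psychological distress" at each site, or 1,000/11 = about 91 from the fixed total. This affects only the degrees of freedom.
- Cost distribution: not given, so normal and log-normal costs were both tried.

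**Number of tests**

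6 × 5 / 2 = 15 pairs.

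**Chance of at least one false difference when all six true means are equal**

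Pairs that share a facility are correlated, so the suitable formula uses the studentized range Q for six groups:

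P(Q(6, df) > √2 × t(0.975, df)), with df = 6 × (n − 1).

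| Patients per facility | df | Chance of at least one false difference |
|---|---|---|
| 10 | 54 | 35.3% |
| 91 | 540 | 36.4% |
| 100 | 594 | 36.4% |
| very large | – | 36.6% |

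Simulation with a separate two-sample t test for each pair (40,000 runs per setting), log-normal costs having log-SD 1.0:

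| Patients per facility | Normal costs | Log-normal costs |
|---|---|---|
| 10 | 36.8% | 28.5% |
| 30 | 36.3% | 31.8% |
| 100 | 36.4% | 33.8% |

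Varying the skew at 100 patients per facility (4,000 runs each) gave 36.6% at log-SD 0.5, 34.1% at 1.0, 29.9% at 1.5 and 23.9% at 2.0. Stronger skew lowers the rate, but every setting stays well above 5%.

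**After the fix**

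A single one-way F test (5 numerator degrees of freedom) at 5%, simulated at 10, 30 and 100 patients per facility, gave a false-positive rate of 5.0% with normal costs and 3.8% to 4.6% with log-normal costs of log-SD 1.0. If all pairs were tested with a Bonferroni adjustment, the level per test would be 0.05/15 = 0.0033.

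**The case against.** The best defence is that this is a wording slip. Facility level is one of the sampling strata, and the intervention is delivered at health centre IIIs and IVs, so a two-group contrast by level may have been meant. The article also names a Kruskal Wallis test for continuous variables elsewhere in its analysis section, so a multi-group test is not foreign to the authors. It is fair to say that the text is ambiguous rather than a firm commitment to 15 unadjusted tests, and that a missing adjustment alone could be left to an analysis plan. The sentence still names six facilities and a two-mean test, and it needs correcting on either reading.

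Several stronger readings are tempting, and the documents do not support them:

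- **That the cost-driver conclusions are compromised.** The Direct costs section derives cost drivers descriptively from cost categories, and uncertainty is handled by best-case and worst-case scenarios. Neither depends on the facility test.
- **That most reported facility differences would be false.** The 36% to 37% is the chance of at least one rejection if all six means are equal; it is not the share of claimed differences that are false. Equal means are also doubtful, because the sites are sampled across facility level and catchment size, and space, utilities and maintenance are site-specific inputs.
- **That the error rate is 54%.** This is 1 − 0.95^15 = 53.7%, which treats the 15 pairs as independent. They overlap, so it does not apply.
- **That costs are known to be strongly skewed.** Stepped care with drugs, referral or bed days for some patients makes a right tail plausible, but the article gives neither a cost distribution nor the share of patients reaching each step.

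**Conclusion.** The sentence is wrong as written: the named test does not match a six-facility comparison, and no two groups are defined. Carried out literally as 15 unadjusted pairwise tests, it gives a chance of at least one false difference of about 36% to 37% with near-normal costs and about 24% to 34% with strongly skewed costs. Those figures assume a two-sided 5% level per test, equal true means and similar facility sizes. They hardly change between 91 and 100 patients per facility.

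The mismatch itself needs none of these assumptions. The consequence is limited to between-facility cost statements in a secondary analysis; the remission outcome and its sample size are untouched.

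**What to change.** Replace the t test with one overall six-group comparison of mean cost per patient: for example a one-way or Welch ANOVA, or a generalised linear model with facility as the only factor. Report each facility's mean with a bootstrap 95% confidence interval. Make pairwise comparisons only with a multiplicity adjustment such as Holm.

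Keep the overall comparison unadjusted for the treatment step reached. That is one of the routes by which facility costs differ, so adjusting for it would remove part of the difference being measured.

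If a two-group contrast such as facility level was intended, name those groups and keep a two-sample comparison.

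The cost is about one sentence in the costing analysis and trivial extra programming on the same data. The downside is that fewer pairwise differences will be nominally significant.
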